### **8.3 Adverse Events**

In order to comply with applicable regulations and Vigilance requirements:

All adverse events and adverse device effects will, at a minimum, be classified in accordance with ISO 14155: 2003 Part 1 and Part 2 and reported according to the Sponsor's internal procedures to investigators, Ethics Committees and Regulatory Authorities.

#### **8.3.1 Definitions**

**Adverse Event:** Any untoward medical occurrence in a patient. This definition does not imply that there is a relationship between the adverse event and the device under investigation.

**Adverse Device Effect:** Any untoward and unintended response to a medical device. This definition includes any event resulting from insufficiencies or inadequacies in the instructions for use or the deployment of the device. It also includes any event that is a result of a user error.

**Serious Adverse Event:** Adverse event that:

- led to a death,
- led to a serious deterioration in the health of the patient that:
  - resulted in a life-threatening illness or injury,
  - resulted in a permanent impairment of a body structure or a body function,
  - required in-patient hospitalization or prolongation of existing hospitalization
  - resulted in medical or surgical intervention to prevent permanent impairment to body structure or a body function
- led to fetal distress, fetal death or a congenital abnormality or birth defect

**Serious Adverse Device Effect:** Adverse device effect that has resulted in any of the consequences characteristic of a serious adverse event or that might have led to any of these consequences if suitable action had not been taken or intervention had not been made or if circumstances had been less opportune.

### 8.3.2 Adverse Event Reporting

The Investigator will monitor the occurrence of adverse events for each patient during the course of the Clinical Evaluation. All adverse events (AEs) reported by the patient, observed by the Investigator, or documented in medical records will be listed on the adverse event case report forms, whether believed by the Investigator to be related or unrelated to the investigational device implant. Beginning with the start of the index procedure, which is defined as the time of the arterial puncture, any new event/experience that was not present at baseline, or worsening of an event present at baseline, is considered an adverse event and should be reported as such.

**Note:** Unchanged, chronic conditions are not adverse events and should not be recorded on the adverse event form of the eCRF.

An adverse event may be expected, (however should still be reported). Expected AEs may include:

Abrupt closure, Acute myocardial infarction, Allergic reaction to contrast, Aneurysm, Arterial perforation, Arterial rupture, Arteriovenous fistula, Arrhythmias (including atrial and ventricular), Bleeding complications (which may require transfusion), Coronary artery spasm, Coronary or stent embolism, Coronary or stent thrombosis, Death, Dissection of the coronary artery, Distal emboli (air, tissue or thrombotic), Drug reactions to anti-platelet agents/contrast medium, Emergent or non-emergent Coronary Artery Bypass Graft Surgery, Fever, Hypotension/Hypertension, Hypersensitivity reactions, Infection and pain at insertion site, Injury to the coronary artery, Ischemia, myocardial, Myelosuppression, Nausea and vomiting, Palpitations, Peripheral ischemia (due to vascular or nerve injury), Pseudoaneurysm, Restenosis of stented segment, Cerebrovascular accident (CVA), Total occlusion of coronary artery, Unstable or stable angina pectoris, Vascular complications (including entry site, which may require vessel repair), Ventricular arrhythmias (including ventricular fibrillation and ventricular tachycardia), Vessel dissection.

Adverse events will be monitored until they are adequately resolved or explained and reported to the DSMB on an ongoing basis throughout the clinical evaluation.

Determination of whether there is a reasonable possibility that an investigational product or device caused or contributed to an AE is to be determined by the Investigator and recorded on the CRFs as **not related, related or unknown**. Determination should be based on assessment of temporal relationships, biologic plausibility, association (or lack of association) with underlying disease, and presence (or absence) of a more-likely cause.

Definitions for determination of the relationship include:

**Not Related:** Exposure to the device has not occurred, or the occurrence of the adverse event is not reasonably related in time, or the adverse event is considered unlikely to be related to the use of the device (biologically implausible).

**Related:** Exposure to the device and the adverse event are reasonably related in time and the device is more likely than other causes to be responsible for the adverse event, or is the most likely cause of the adverse event.

**Unknown:** Exposure to the device and the occurrence of adverse event cannot be reasonably determined to be unrelated to the device. If the relationship is identified as unknown it will be treated as related to the device.

If any adverse event is considered related to the administration of the device, that event will be followed until resolution or the Investigator judges the event to be chronic or stable.

## ***8.4 Serious Adverse Events***

Each adverse event or complication meeting the definition for serious adverse event **whether or not considered device-related** should be considered as such and reported to Sponsor **within 24 hours of knowledge of event by entering the event into the electronic database**. The completion of an Adverse Event / Serious Adverse Event (AE/SAE) form in the eCRF will trigger an e-mail notification to Sponsor containing the event information. The investigator will report the event to the EC according to the institution's reporting requirements.

Reports relating to the patient's subsequent medical course must be submitted to Sponsor until the event has subsided or, in case of permanent impairment, until the event stabilizes and the overall clinical outcome has been ascertained.

Sponsor will ensure that all SAEs are reported to the relevant authorities and Principal Investigators according to relevant regulations and that product experience handling reporting requirements are followed.

Note: All device malfunctions should be reported to the Sponsor within 24 hours of knowledge.

## ***8.5 Safety Monitoring***

### **8.5.1 Data Safety Monitoring Board (DSMB)**

All adverse events will be reported to the DSMB (Data and Safety Monitoring Board) and reviewed on a regular basis. The DSMB is an independent committee that will be comprised of at least three members, typically composed of at least two interventional cardiologists and a biostatistician. The DSMB members will not have any affiliation with the Sponsor, the Investigator, the Core lab or the clinical evaluation sites. The DSMB may request additional information as needed. Based on safety data, the DSMB may recommend that the Steering Committee modify or stop the study. All final decisions, however, regarding study modifications, rest with the Steering Committee. No formal statistical rule for stopping the study will be defined.

## ***8.6 Adjudication of Events***

### **8.6.1 Clinical Events Committee (CEC)**

The Clinical Events Committee (CEC) is an independent adjudication body comprised of interventional and/or non-interventional cardiologists who are not participants in the clinical evaluation.

The CEC will review and adjudicate all endpoint related and major bleeding and vascular events according to the definitions provided in Appendix II. These definitions are based on the definitions developed by the Academic Research Consortium (ARC), as published in *Circulation* (Cutlip, D.E., et al., Clinical End Points in Coronary Stent Trials: A Case for Standardized Definitions. *Circulation*, 2007. 115: p. 2344-2351.)

#### **- Deaths**

The Clinical Events Committee (CEC) will adjudicate all patient deaths.

#### **- Myocardial Infarctions**

The CEC will adjudicate all possible cases of Q wave or non-Q wave myocardial infarctions for confirmation and outcomes/treatment.

- **Revascularizations**

For the SPIRIT WOMEN Single Arm Study, the CEC will be responsible for reviewing all angiograms to determine if a revascularization was performed, and if so, whether or not the revascularization was related to the target lesion, target vessel or non-target vessel. All revascularizations will be considered clinically indicated. For the randomized sub-study, the Angiographic Core Laboratory will evaluate whether the revascularization was performed and related to the target lesion, target vessel or non-target vessel and will provide QCA assessment of diameter stenosis. Based on that and clinical information the CEC will adjudicate whether the revascularization was clinically indicated or not.

- **Stent Thrombosis**

The CEC will adjudicate all possible cases of stent thromboses for confirmation and outcomes/treatment.

- **Vascular and Bleeding Complications**

The CEC will adjudicate all vascular and bleeding complications for confirmation and outcomes/treatment.

- **Other Adverse Events**

Adverse events other than the above will not be provided to the CEC for adjudication and will be reviewed by the Data Safety Monitoring Board (DSMB).

## **9 STATISTICAL ANALYSIS**

### ***9.1 Statistical Overview***

This trial is composed of two parts:

#### **SPIRIT WOMEN Single Arm Study:**

A prospective, open-label, single arm, multi-center study evaluating performance of the XIENCE EECSS in the treatment of female patients according to IFU.

#### **Randomized sub-study:**

A prospective, single-blind, double arm, randomized, multi-center study comparing the XIENCE EECSS (XIENCE V EECSS and XIENCE PRIME EECSS) to the CYPHER SELECT™ Plus Sirolimus-eluting Coronary Stent.

The primary endpoint of this clinical evaluation is Adjudicated Composite rate of all Death, all Myocardial Infarction (MI) and Target Vessel Revascularization (TVR) at 1 year.

Descriptive analysis will be provided for the primary endpoint.

Hypothesis testing will be performed on the secondary endpoint in-stent Late Loss at 270 days. The null ( $H_0$ ) and alternative ( $H_A$ ) hypotheses are:

$$\begin{aligned} H_0: & \text{In-stent LL}_{\text{XIENCE}} - \text{In-stent LL}_{\text{CYPHER}} \geq \delta \\ H_A: & \text{In-stent LL}_{\text{XIENCE}} - \text{In-stent LL}_{\text{CYPHER}} < \delta \end{aligned}$$

where  $\delta$  is the non-inferiority margin.

## **9.2 Sample Size Justification**

The SPIRIT WOMEN Clinical Evaluation aims to characterize the female population undergoing stent implantation and to precisely estimate the performance of XIENCE EECSS in this specific population. The primary endpoint is Adjudicated Composite rate of all Death, all Myocardial Infarction (MI) and Target Vessel Revascularization (TVR) at 1 year.

A sample size of 1550 patients enrolled in the SPIRIT WOMEN Single Arm Study will produce a narrow two-sided 95% confidence interval around the clinical endpoint estimates. The ½ width of the 2-sided confidence interval around the 1 year primary endpoint estimate will be between 1.5% and 1.7% assuming the true rate between 10% and 14%.

Moreover the pooled analysis including patients from the Single Arm Study and patients from the randomized sub-study who were randomized to XIENCE EECSS will report on approximately 1850 patients.

A drop-out rate of 3% is expected at 1-year.

### **Randomized Sub-study:**

The overall sample size for the randomized sub-study is based on the main secondary endpoint of in-stent Late Loss at 270 days.

The sample size calculation is based on the following assumptions:

One-tailed non-inferiority test

$\alpha = 0.05$

Power = 90 %

Randomization ratio is 2 (XIENCE EECSS arm) : 1 (CYPHER arm)

True mean in-stent Late Loss is assumed to be equal for both treatment arms

Standard deviation is assumed to be 0.53 mm in both XIENCE EECSS arm and CYPHER arm

Non-inferiority margin delta ( $\delta$ ) of 0.17 mm

Given the above assumptions, approximately 252 subjects in the XIENCE EECSS arm and 126 subjects in the CYPHER arm will be required. In order to account for dropouts and to ensure enough angiographic data, approximately 450 subjects will be enrolled, of which approximately 300 will be in the XIENCE EECSS arm and approximately 150 in the CYPHER arm.

## **9.3 Analysis Populations**

### **9.3.1 Intent to Treat Population**

The intent-to-treat population for the randomized sub-study will consist of all patients (all lesions) randomized, regardless of the treatment actually received. Subjects will be analyzed in the treatment arm to which they were randomized.

**Analysis for the Single Arm Study will be performed on the intent-to-treat population which will include all patients**

1. who have signed the Patient Informed Consent
  2. who have been registered in the ICON IVRS system
- AND
3. who comply to at least one of the following:
    - a. at least one XIENCE V stent has been implanted

- b. a non-XIENCE V stent has been implanted after an intention to or an attempt made to implant a XIENCE V
- c. no stent was implanted after an intention to or an attempt made to implant a XIENCE V

Patients not meeting the above criteria will not be required to undergo follow up as mandated by the CIP

Adverse event reported for patients who comply to criteria numbers 1 and 2 as mentioned above will be adjudicated but not included in the analysis even if criterion number 3 is not met.

Lesions for which there was no attempt to implant a XIENCE V EECS and lesions located in a bypass graft will not be considered in the analysis for the Single Arm Study.

For the pooled analysis the intent-to-treat population will consist of the intent-to-treat population in the SPIRIT WOMEN Single Arm Study and patients from the intent-to-treat population in the randomized sub-study who were randomized to XIENCE EECS.

### **9.3.2 Per-Treatment Evaluable Population**

In the randomized sub-study, the per-treatment evaluable population will consist of patients who have received the study device at the target lesion(s), who have no major procedural protocol deviations (e.g. stent implanted in a non-native coronary artery) other than those relating to treatment arm (randomized versus actually received) and for whom follow-up data is available. For example, if a patient had a stent placed in a saphenous vein graft, she would be excluded from the per-treatment evaluable population.

Analyses based on the per-treatment evaluable population will be “as treated”. Patients will be included in the treatment arm corresponding to the study stent actually received.

Patients receiving a non-study stent on one or more of the target lesions or receiving several types of stents at target vessels will be excluded from this population.

No per-treatment evaluable population is defined for the SPIRIT WOMEN Single Arm Study.

## ***9.4 Statistical Analyses***

All analyses for SPIRIT WOMEN Single Arm Study and randomized sub-study will be performed on the intent-to-treat population. Additionally for the randomized sub-study the primary and secondary endpoints will be analyzed on the per-treatment evaluable population.

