### **Additional treatment strategy for patients enrolled in the randomized sub-study is as follows:**

The test devices used are the XIENCE V Everolimus Eluting Coronary Stent System (XIENCE V EECSS) and the XIENCE PRIME Everolimus Eluting Coronary Stent System (XIENCE PRIME EECSS).

After meeting the general and angiographic inclusion and exclusion criteria, the target lesion(s) should be treated according to the same randomization schedule. If two or more target lesions are to be treated, all lesions must receive the treatment that has been assigned as per the randomization.

If two or more target lesions are to be treated and the patient is randomized to the XIENCE EECSS, all lesions must receive either the XIENCE V EECSS or the XIENCE PRIME EECSS.

Randomization should be done only after confirmation of the angiographic inclusion criteria and before implantation of the first stent. Once randomization is completed and a treatment is assigned, crossover is not permitted.

If it is not possible to implant the stent allocated by randomization, it is recommended that any other commercially available stent, either BMS or DES be implanted, rather than the XIENCE or the CYPHER SELECT™ Plus Sirolimus-eluting Coronary Stent.

If bailout stenting is necessary, the stent used should be the same as allocated by randomization for the index procedure, and should be used according to the Instructions for Use (IFU).

If any staged procedures are planned at baseline, it is necessary that the investigator treats the enrolled patients with the same study stent during the planned staged procedure as was used at baseline (as allocated at randomization).

All patients should receive  $\geq 75$  mg of aspirin daily for a minimum of five years following the procedure.

All patients should receive clopidogrel 75 mg daily for a period of at least 6 months. Ticlopidine at a dose standard with hospital practice may be substituted for clopidogrel, as required by hospital practice or if the patient develops hypersensitivity to clopidogrel.

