### **Randomized Sub-study – Analysis of In-stent Late Loss at 270 days**

Statistical testing of the in-stent Late Loss endpoint will be one-tailed and performed at the 0.05 significance level for the comparison of XIENCE arm to CYPHER arm. The hypothesis testing will be based on all target lesions in the intent-to-treat population. The null hypothesis will be evaluated using a

non-inferiority test with asymptotic test statistic. If the correlation between lesions within patients is large, then repeated measures analysis will be considered.

If non-inferiority is shown and the in-stent Late Loss is lower in the XIENCE arm, then superiority analysis might be performed using a two-sided t-test at the 5% level.

In case the use of parametric tests is inappropriate due to the distribution assumptions violation, non-parametric tests will be considered.

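### Sub-study non-inferiority is decided in the ITT population alone; the per-treatment analysis has no role in the decision and regroups crossovers by stent received

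*Protocol*

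**What the plan says.** All references are to the protocol.

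- **Decision population.** Section 9.4 (late loss analysis): "The hypothesis testing will be based on all target lesions in the intent-to-treat population". The summary table names ITT as the primary population for every endpoint, and section 9.4 ties success of the sub-study to this one test.
- **ITT arms.** Section 9.3.1 keeps every randomized patient, with all lesions, in the arm assigned, whatever was implanted.
- **Substitution.** If the allocated stent cannot be implanted, section 4.2 says "it is recommended that any other commercially available stent, either BMS or DES be implanted", in preference to either study stent. Crossover is not permitted.
- **Per-treatment set.** Section 9.4: "Additionally for the randomized sub-study the primary and secondary endpoints will be analyzed on the per-treatment evaluable population". Section 9.3.2 removes patients with a non-study stent at any target lesion or with several stent types. A mismatch between assigned and received arm is not a reason for removal: "Patients will be included in the treatment arm corresponding to the study stent actually received".
- **Who has a late loss value.** Section 8.2 limits mandatory follow-up angiography to patients with at least one study stent. Section 9.6 analyses available data only.

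**The concern.** In a superiority trial, dilution from non-adherence works against the claim. In a non-inferiority trial it works for it: if XIENCE were truly worse, every lesion that did not get its assigned stent would tend to shrink the observed difference and make the margin easier to meet. A second population that received the assigned devices is the usual safeguard. Here it is computed but has no stated consequence, and the text does not say how a discordant result is read.

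The safeguard is also weaker than it could be. A patient randomized to one study stent who received the other is counted in the second arm, so the two groups are partly defined by what happened after randomization.

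At stake is the one confirmatory conclusion of the sub-study, since the primary clinical endpoint is only described.

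**Working it through.** **Inputs from the protocol.** Section 9.2: margin 0.17 mm; "Standard deviation is assumed to be 0.53 mm in both XIENCE EECSS arm and CYPHER arm"; "True mean in-stent Late Loss is assumed to be equal for both treatment arms"; 2:1 allocation; power 90%; 252 + 126 = 378 evaluable, about 450 enrolled. Section 9.4: the test is "one-tailed and performed at the 0.05 significance level for the comparison of XIENCE arm to CYPHER arm".

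**Assumptions, because the documents give no rates.** f is the share of evaluable lesions in each arm that carry the same substitute stent. c is the share in each arm that received the other study stent. One value per subject is used, as in the sample size calculation, and the SD stays at 0.53 mm.

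**1. The plan's own figure.** Control n = (1.645 + 1.282)^2 x 0.53^2 x 1.5 / 0.17^2, about 125, so 125 + 250. With the noncentral t distribution, 126 + 252 gives power 0.9014 and 125 + 250 gives 0.8994. The stated 126 + 252 is reproduced.

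**2. Standard error.** 0.53 x sqrt(1/252 + 1/126) = 0.0578 mm.

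**3. Equal dilution.** Let the true on-treatment difference equal the margin, so a correct test passes 5% of the time. The ITT difference becomes 0.17 x (1 - f), and the pass probability is Phi(-1.645 + 0.17 f / 0.0578).

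| f | shift (mm) | type I error |
|---|---|---|
| 0 | 0 | 5.0% |
| 2% | 0.0034 | 5.6% |
| 5% | 0.0085 | 6.7% |

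**4. Symmetric crossover.** The ITT difference becomes 0.17 x (1 - 2c).

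| c | shift (mm) | type I error |
|---|---|---|
| 1% | 0.0034 | 5.6% |
| 2% | 0.0068 | 6.3% |
| 5% | 0.0170 | 8.8% |

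**5. Cost of requiring both sets.** Suppose a share of the 378 evaluable subjects leaves the per-treatment set, the true difference is zero in both sets, and the two test statistics have correlation sqrt(1 - share), which is an assumption.

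| share leaving | power, ITT | power, per-treatment | power, both |
|---|---|---|---|
| 2% | 0.902 | 0.897 | 0.890 |
| 5% | 0.902 | 0.889 | 0.879 |

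To keep 378 subjects in the per-treatment set, 378/0.98 = 386 or 378/0.95 = 398 ITT-evaluable subjects are needed. At the plan's own allowance (1 - 378/450 = 16%), that is about 460 or 474 enrolled.

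**The case against.** **Most substituted patients never reach the test.** A patient who received only a non-study stent is not due for the 270-day film (section 8.2), and without a film she is dropped (section 9.6). This stands. What remains in the ITT test is multi-lesion patients with one study and one non-study stent, crossovers, and occasional clinically driven films. The shares in the working apply to evaluable lesions and should be read with that limit in mind.

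**A reader might infer a much larger error.** Section 2.1.1 gives 0.10 mm as an 88% reduction in the first XIENCE V trial, so bare metal late loss is about 0.10/0.12 = 0.83 mm. If 3% or 5% more control than XIENCE lesions carried bare metal stents, the control mean would rise by 0.022 or 0.037 mm, and the type I error would be about 10% or 16%. The arithmetic is right, but the documents do not support these as expected sizes. They give no rate and no reason to fix the direction; an excess in the XIENCE arm would bias against XIENCE. Substitutes may also be drug-eluting, the 0.83 mm comes from a 60-patient trial, and the 0.10 mm used as control level is XIENCE V's value (the CYPHER values quoted are 0.09, 0.13 and 0.19 mm). These figures are worst-case illustrations only.

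**Crossover is prohibited and should be rare.** True, so the as-treated issue may touch few patients. Section 9.3.2 nevertheless provides for them. Excluding them also conditions on a post-randomization event and does not restore a fully randomized comparison; it only ensures that nobody is counted in an arm to which she was not assigned.

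**The per-treatment result will be reported, and the analysis plan may say how to read it.** A discordant result would be visible. But the protocol itself fixes ITT as the basis for success, so an explanatory rule elsewhere would not change the decision.

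**The change has a price.** It does: 252 + 126 was sized for one test.

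**Conclusion.** The point holds in a limited form. The protocol decides non-inferiority in ITT alone, gives the per-treatment analysis no role in the decision, and forms that set's arms partly by treatment received. Success would therefore be declared even if the per-treatment result missed 0.17 mm.

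The likely size is modest. Type I error is about 5.6-6.7% under an assumed equal dilution of 2-5% of evaluable lesions, and about 5.6-8.8% under an assumed symmetric crossover of 1-5%, against a nominal 5%. Both ranges rest on assumed rates, a true on-treatment difference at the margin, and 378 evaluable subjects.

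It would go too far to say that the ITT analysis is wrong or that the sample size is in error: the stated figure reproduces, and the per-treatment set already excludes patients with non-study stents. This is an inexpensive strengthening of the decision rule.

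**What to change.** In section 9.4, state that non-inferiority is declared only if the upper one-sided 95% confidence limit for the late loss difference lies below 0.17 mm in both the ITT and the per-treatment evaluable populations, and that a pass in only one is not a success. No alpha adjustment is needed, because both must pass.

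In section 9.3.2, exclude patients who received the other study stent from the per-treatment set instead of moving them to that arm.

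In section 9.2, restate the power for the joint rule under a stated assumption about losses from the per-treatment set: about 0.89 at 2% and 0.88 at 5%. The sponsor can accept this or enrol about 460 or 474 instead of 450 to keep 378 subjects in that set.

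Both analyses are already planned, so apart from this choice only wording changes. No change to the stent-substitution rule is proposed.
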